**Data management post-project completion**

After completion of the trial, the data will be continued to be stored on Qualtrics. Only the PI MJ and CI KT will have access to the data after the trial. Following the National Health and Medical Research Council (NHMRC) guidelines for clinical trials, data will be retained for 15 years and then securely destroyed. Files will be destroyed according to the University of South Australia Policy Ownership and Retention of Data (Policy No: RES-17.0)

**Data analysis**

**Qualitative data analysis**

The qualitative data from interviews will be analysed using thematic analysis (27). The planned data analysis will encompass the processes of immersion in the data set, coding to generate preliminary codes, the development of tentative themes, and reflection upon and revision of themes. This will be followed by a description of the themes and sub-themes. The interview transcripts will be examined thematically across the entire data set as well as based on each interview. Codes and themes will be validated by an independent researcher at key points in the analysis. NVivo Pro software version 12 or Qualtrics online survey platform will be employed to facilitate coding (28).

**Quantitative data analysis**

We will describe the demographic characteristics of the custodial health nurses and the people in custody using Microsoft Excel software (29) or the IBM SPSS Statistics software version 29 (30). The descriptive data will be presented and reported using mean, standard deviation, median, and range or counts and percentages.

**Statistical analyses**

All data will be entered and analysed descriptively. The primary analysis is intended to determine whether conducting a subsequent fully powered RCT is feasible. Therefore, the analyses will be descriptive by exploring all feasibility outcomes and will include measures of uncertainty, such as 95% CIs. As feasibility trials are not designed to establish efficacy, we will estimate the variance of outcome measures and calculate the effect size differences (with 95% CIs) on outcome measures from baseline to both follow-up points (on an intention-to-treat basis) in both groups. Where appropriate, the generalised estimating equation (GEE) will be employed to analyse the preliminary effects of BA across the two time points (baseline and 6 weeks). The GEE analysis will account for intra-correlated repeated outcome data and accommodate data missing at random.

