**Method**

A sample of 60 people in custody aged over 18 years or older with presenting symptoms of depression as assessed using the PHQ 9 scale (with a score of 5-14 mild to moderate depression) will participate in the trial. Recruited people in custody will be randomised to receive BA plus treatment as usual (TAU) or TAU for depression provided by custodial health nurses. Eight custodial health nurses will be recruited from four rural prisons in South Australia. The custodial health nurses will be prepared to deliver Behavioural Activation to people in custody at the selected prisons. The BA intervention will involve preparing people in custody to monitor their mood, identify triggers that can impact mood, identify activities that may enhance mood, and enable each participating person in custody to formulate an activity schedule. BA will involve twelve conversations with people in custody held twice weekly over six weeks. Changes in depressive symptoms and health-related quality of life will be assessed at three-time points: (a) at baseline, (b) 6 weeks, and (c) 3 months post-intervention. We will use descriptive statistics to report changes over time, but not make any judgement. In addition, we will interview custodial health nurses and people in custody to understand further BA acceptability and feasibility in prison settings.

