**AIMS**

We will examine the feasibility and acceptability of:

1. Telehealth BA plus usual SA prison health care (intervention) compared to usual SA prison health care alone (treatment as usual (TAU)) in the treatment and management of depression in people in custody who have been diagnosed with a mood disorder.
2. Telehealth BA plus usual SA prison health care (intervention) compared to usual SA prison health care alone (TAU) in improving the quality of life of people in custody who are diagnosed with clinically meaningful depressive symptoms.

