**Evaluation**

**Feasibility**

The study feasibility outcomes will be evaluated as follows:

- Determine the proportion of eligible people in custody with depressive symptoms who are approached and agree to participate in the trial.
- Determine the proportion of eligible people in custody who have agreed to participate and agree to be randomised.
- Determine the proportion of people in custody with depressive symptoms that complete baseline measures.
- Determine the proportion of people in custody who complete a co-delivered Tele-trial Behavioural Activation treatment (attending for a minimum of six sessions over six weeks).
- Determine the proportion of people in custody who complete outcome measures at six weeks and three-month follow-up.
- Establish SAPHS nurses’ fidelity to Behavioural Activation treatment.
- Calculate the preliminary efficacy of Behavioural Activation on the primary clinical outcome measure.
- Explore SAPHS nurses’ experiences of delivering a co-delivered tele-trial Behavioural Activation treatment to the people in custody.
- Explore SAPHS nurses’ experiences receiving co-delivered tele-trial Behavioural Activation training and supervision.
- Determine the proportion of people in custody with depressive symptoms that participate in the tele-trial improve their health-related quality of life outcomes (clinical outcome measure).
- The number of adverse events and harms that occur during the trial.

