**Preliminary intervention effects (primary and secondary outcomes)**

**Clinical outcome measure- depression**

The first clinical outcome will be a change in depressive symptoms as assessed by the tele-trial research nurse using the PHQ-9 scale.

*Primary Health Questionnaire Nine (PHQ 9)*. Depressive symptoms will be measured with the Primary Health Questionnaire Nine (PHQ 9) (21, 22). The PHQ 9 is a 4-point Likert-type scale (0, absent; 1, mild; 2, moderate; 3, severe) with nine items that correspond to the DSM-IV Diagnostic Criterion A symptoms for major depressive disorder (23). A meta-analysis rated the PHQ-9 scale as being reliable with a sensitivity of 88% and a specificity of 78% at a cut-off of 10 or above (24).

The clinical outcome measure will be implemented at three-time points (a) at baseline (0 weeks), (b) at 6 weeks post-intervention, and (c) at 3 months post-intervention.

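### The planned effect size runs from baseline to follow-up in each group, and no BA-minus-TAU contrast is named: state a baseline-adjusted between-arm difference

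*Protocol*

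**What the plan says.** The effect measure for the clinical outcomes is set in one sentence of Statistical analyses: the team will calculate "effect size differences (with 95% CIs) on outcome measures from baseline to both follow-up points", by intention to treat, in both groups. The next sentence adds a GEE, to be used where appropriate, "to analyse the preliminary effects of BA across the two time points (baseline and 6 weeks"). It names no model terms.

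Three other places bear on the reading:

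- The Method paragraph of the abstract: "We will use descriptive statistics to report changes over time, but not make any judgement".
- Clinical outcome measure- depression: "The first clinical outcome will be a change in depressive symptoms", measured with the PHQ-9.
- Evaluation, Feasibility: the list includes "the proportion of people in custody with depressive symptoms that participate in the tele-trial improve their health-related quality of life outcomes". It gives no arm, time point, SF-36 scale or threshold.

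The AIMS section sets out a comparison: BA plus usual care "compared to usual SA prison health care alone (treatment as usual (TAU")). The Discussion says that the effect size, together with effect sizes from other studies, will help to set the sample size of a full-scale trial.

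**The concern.** The trial randomises so that BA can be compared with TAU, but the sentence that fixes the effect measure describes movement from baseline in each group and names no contrast between the groups. A change within the BA arm adds together natural course, usual care, regression to the mean and any effect of BA. Only the comparison with TAU separates the last of these.

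The analysis is descriptive, so no efficacy conclusion is at stake. What is at stake is the figure carried into the planning of the next trial. If that figure is a within-arm change, the next trial may be planned too small. If it is an unadjusted difference in change, the estimate is sound, but its interval is wider than it need be with only 30 per arm.

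The SF-36 item in the feasibility list has a related weakness. With no threshold, any upward movement counts as improvement. If change were symmetric around zero, about half of each arm would improve with no effect at all.

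**Working it through.** **Inputs from the protocol.** Sample size: 30 per arm, 2 × 30 = 60, which reproduces the stated target. Follow-ups: 6 weeks and 3 months. Entry range: PHQ-9 of 5 to 14. The protocol gives no SD, no baseline-to-follow-up correlation r, no target effect and no power. Every value of these below is an assumption.

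**1. Within-arm reading: what it measures.** In a 20,000-run simulation with 30 per arm, r = 0.5, equal SDs and a true BA effect of zero:

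| Natural improvement (assumed) | Mean within-arm change, BA arm | 95% CI of that change excludes 0 | Mean BA-minus-TAU difference in change | 95% CI of that difference excludes 0 |
|---|---|---|---|---|
| 0 | 0.00 SD | 5% | 0.00 | 5% |
| 0.3 SD | 0.30 SD | 35% | 0.00 | 5% |
| 0.5 SD | 0.50 SD | 76% | 0.00 | 5% |

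The within-arm figure returns whatever natural course was put in. The between-arm difference stays centred on zero.

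**2. Within-arm reading: effect on planning.** Suppose BA changes by 0.6 SD and TAU by 0.3 SD, so that the BA effect is 0.3 SD. With n per arm = 2 × (1.96 + 1.2816)² / d², two-sided 5% and 90% power:

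- d = 0.6: 2 × 10.507 / 0.36 = 58.4, so 59 per arm.
- d = 0.3: 2 × 10.507 / 0.09 = 233.5, so 234 per arm.
- Power of 59 per arm at d = 0.3: Φ(0.3 × √(59/2) − 1.96) = Φ(−0.33) = 37%.

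**3. Difference-in-change reading: precision with equal SDs.** Per-person variance in SD² units is 2(1 − r) for a change score and 1 − r² after baseline adjustment. The ratio is 2/(1 + r). The 95% half-width of the between-arm difference is 1.96 × √(2 × variance / 30).

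| r (assumed) | Change score | Baseline-adjusted | Variance ratio | n per arm for change score to match 30 adjusted |
|---|---|---|---|---|
| 0.2 | 0.64 SD | 0.50 SD | 1.67 | 50.0 |
| 0.5 | 0.51 SD | 0.44 SD | 1.33 | 40.0 |
| 0.8 | 0.32 SD | 0.30 SD | 1.11 | 33.3 |

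**4. The same reading for the PHQ-9.** Entry at 5 to 14 makes the baseline SD smaller than the follow-up SD, so equal SDs do not apply. If the unrestricted SD is σ at both times, the unrestricted correlation is r and the baseline SD after selection is s, the variance ratio becomes 1 + (s/σ)² × (1 − r)/(1 + r). With an assumed population mean of 9 and σ = 5.5, s is about 2.72 and (s/σ)² = 0.245. The ratio is then 1.08 at r = 0.5 and 1.04 at r = 0.7. Over r = 0.2 to 0.8 it runs from 1.16 to 1.03.

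**5. Does the GEE supply the contrast?** It would if it held a group-by-time term or its equivalent. No such term is stated, use of the model is conditional, and it covers baseline and 6 weeks only. Even on a favourable reading, the 3-month result rests on the effect-size sentence alone.

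**The case against.** The strongest reply is that the sentence is only loosely worded. The phrase about effect size differences can mean the difference between arms in change from baseline. Natural course then cancels, the estimate is unbiased under randomisation, and only precision is lost, which for the PHQ-9 may be slight. A GEE for the effects of BA in a two-arm randomised trial would naturally contain a between-arm contrast, and model terms are commonly left to an analysis plan that is not shown here. The trial also disclaims any test of efficacy, and its effect size is only one input to the next trial's size.

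Most of this stands. The text does not commit the team to within-arm effect sizes, and the absence of a model specification is not the complaint. What remains is that the protocol does state an effect measure, from baseline and in both groups, and that one ordinary reading of it does not answer the stated aim. The GEE cannot remove that ambiguity at 3 months.

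Two stronger inferences are tempting but unsupported:

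- A reader might infer that range restriction will inflate the effect size through a small baseline SD. The protocol names no standardiser, and does not say that the effect size is standardised.
- A reader might infer that regression to the mean will make BA look good. Under the assumptions in step 4 the selected baseline mean is about 9.38, so with r = 0.5 it accounts for only 0.5 × (9.38 − 9) = 0.19 points. With a population mean of 11 the selected mean is about 9.87 and the shift runs the other way.

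Nor does the SF-36 proportion replace a continuous analysis. The effect-size sentence covers all outcome measures, so the proportion is an addition.

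**Conclusion.** The point holds as an ambiguity that should be removed, not as a proven error in the estimate. The stated effect measure allows a reading that is not an effect of BA, and nowhere does the protocol name the BA-minus-TAU difference that its aims call for.

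The size depends on which reading was meant. Under the within-arm reading, the planning figure absorbs all of the change seen under usual care; in the example, the next trial would have 37% power in place of 90%. Under the difference-in-change reading there is no bias, and the cost is 11% to 67% more variance with equal SDs (r from 0.8 to 0.2), and perhaps only a few percent for the PHQ-9. All SDs, correlations and effects here are assumed, and the effect on the next trial is tempered because other studies' effect sizes will be used as well.

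**What to change.** In Statistical analyses, replace the effect-size sentence with wording such as: for the PHQ-9 and for the SF-36 scores, the effect estimate is the BA-minus-TAU mean difference at 6 weeks and at 3 months, adjusted for the baseline value of the same scale, in scale points with 95% CI, by intention to treat; changes within each arm are reported as description only. A GEE that uses all three time points and yields the same contrast would serve equally well. The current two-time-point wording should then be aligned with it.

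In Evaluation, Feasibility, report the SF-36 result as that same adjusted mean difference, in place of the undefined proportion who improve.

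The cost is wording only. Baseline scores are already collected, the sample stays at 60, and no new data are needed.

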
**Dissemination**

We will report findings from the present study using the Consolidated Standards of Reporting Trials (CONSORT) framework for reporting randomised pilot and feasibility trials (31). We intend to publish the findings in peer-reviewed journals. Authorship of any publications will be determined using the recommendations of the International Committee of Medical Journal Editors concerning authorship (32). Findings will also be presented at relevant seminars and professional conferences. Additionally, the participating prison sites will be provided with a summary of the findings for distribution to participants and relevant stakeholders. Public access to the study protocol will be ensured via the publication of the protocol in a professional peer-reviewed journal and registration of the trial protocol in the Australian New Zealand Clinical Trials Registry (ANZCTR) (33).

**Ethical considerations**

Ethical approval for the study will be sought from the Central Adelaide Local Health Network and the University of South Australia Human Research Ethics Committees. The study will be informed by the principles of Good Clinical Practice (GCP) enshrined in the “Declaration of Helsinki”, the Australian Code for the Responsible Conduct of Research, and the Australian Clinical Trial Handbook (34-36). The study may establish the feasibility of preparing custodial health nurses to deliver BA to people in custody with depression. If feasible, this will allow the research team to conduct an effectiveness study to assess if BA is clinically effective for people in custody with depression. The effectiveness study will also include a cost-benefit analysis. The outcomes of this program of work may increase access to an evidenced-based psychological treatment for depression to support people in custody. The benefits for the custodial health nurses include access to support and supervision from the BA experts which will enhance skills development. For the people in custody with depressive symptoms, the anticipated benefits include access to alternative psychotherapy which may reduce depressive symptoms.

Potential participants will be aware that their participation is entirely voluntary and that they may withdraw from the study at any point. Recruitment will be conducted by the tele-trial research nurse not working at the service provider to minimise the risk that people in custody may feel coerced to take part. People in custody will be given the opportunity, if required, to discuss the study with others who are important to them before consenting to take part in the trial. The potential benefits and risks of participation in the trial will be explained in Participant Information Sheets. Discussion of depression usually evokes emotive feelings. Participants will be provided with information about how they can access support.

The privacy of people in custody will be managed in a manner consistent with existing SA Prison Health Service arrangements. The intervention will be delivered at the prison health care centres and unless the prisoner discloses to other prisoners that they are attending the health centre for behavioural activation, the other prisoners will not be aware.

BA will be delivered by the custodial health nurses who will be responsible for recognising, responding, and reporting any distress arising from the intervention. The custodial health nurses will receive ongoing clinical supervision from telehealth BA experts who will have adequate professional indemnity insurance. After each prisoner has completed each session of BA, the custodial health nurses will ask them about their emotional well-being and if they have experienced any distress. If distress is experienced, the people in custody will have access to ongoing support through their existing support team and will be aware of how to contact this team. We have developed a distress protocol for people in custody (Attachment XIX). Any modifications to the protocol will be advised to the ethics committee and the Australian New Zealand Clinical Trials Registry (ANZCTR) (33), accordingly.

**Patient and public involvement**

An advisory committee will be established to develop, refine, and review the study recruitment materials. This will comprise prison advocacy groups from the four sites. We will ask the prison advocates for advice on interpreting the interviews we conduct with people in custody and advice on how best to share the findings with other patient public involvement groups who support people in custody.

**Safety considerations**

As noted, BA has not been conducted in SA prisons before. Thus, our safety considerations have been informed by other studies conducting similar interventions in community dwellings. An RCT study investigating the cost-effectiveness of BA compared with CBT for adults with depression reported that depression-related, but not treatment-related, serious adverse events occurred in three participants in the BA group and eight participants in the CBT group (37). The workers who delivered BA in the study were not specialist mental health workers, but university graduates who completed a five-day training program in BA.

To mitigate the risk of adverse effects we will put in place several procedures. We will ensure that custodial health nurses engage the people in custody at each assessment or the start of each BA session to check how they are feeling and if they experienced any unexpected effects of the intervention.

Custodial health nurses may find it distressing to work with people in custody with depression. Opportunities will be provided for the custodial health nurses to debrief with the BA experts via the telehealth supervision and support structure. In addition, all custodial health nurses will be invited to attend monthly supervision sessions with the BA experts. See also the Distress Protocol for custodial health nurses (Attachment XIX).

We will report all adverse events to the trial steering committee. If the trial steering committee considered that adverse events are a result of the intervention, we will suspend the trial. Adverse events will be analysed and where related to delivery mechanisms, will inform modifications to future trials.

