**Intervention**

**BA tele-trial intervention group**

We will recruit approximately 30 people in custody in the intervention group who will receive BA plus usual prison health care (20). The intervention will be delivered by the custodial health nurses who will receive ongoing clinical supervision from an expert in BA via a telehealth video link. The people in custody will be offered twelve sessions of BA, which will be delivered twice weekly, in 30-minute sessions, for six weeks. Specific BA techniques that will be applied include (a) identification of depressed behaviours (b) analysis of the triggers and consequences of depressed behaviours (c) monitoring of activities (d) development of alternative goal-orientated behaviours (e) scheduling of activities, and (f) the development of alternative behavioural responses to rumination.

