**TAU group**

People in custody allocated to the control group will receive the usual prison health care alone. No other specific intervention will be provided to this group. Across sites, TAU will be composed of 30 participants (20).

The CONSORT diagram illustrating participant flow is shown below (Figure I).

[figure not shown]

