**Clinical outcome measure- quality of life**

The second clinical outcome will be the level of health-related quality of life as measured by the 36-Item Short Form Health Survey (SF 36) (25) The SF 36 measures physical functioning, role physical, bodily pain, general health, vitality, social functioning, role emotion, and mental health (25). In this study, we will administer the SF 36 questionnaire at three-time points: (a) at baseline (0 weeks), immediately after postintervention (6 weeks), and (c) at three months post-intervention.

Completion of eight (8) out of 10 sessions will be deemed to constitute treatment engagement and completion. Acceptability of the treatment will be determined from perceptions of satisfaction with and benefits from the BA treatment obtained through interviews with people in custody.

Other data to be collected

*Sociodemographic Questionnaire*

Demographic information about gender, date of birth, marital status, educational level and type of prison pathway the person in custody is located will be collected by the tele-trial research nurse at the assessment and recruitment stage (Attachment XVII).

*Contextual factors*

We will collect information about each participating tele-trial site at baseline and 6 weeks post-intervention. The information will be important in understanding the implementation process. These factors (including organisational changes, staffing changes, etc), will be collected by the tele-trial research nurse through conversations with the custodial health nurses and the nurse unit managers at the four participating prisons.

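### Scheduled enquiry about adverse events is far more frequent in the BA arm than in TAU, and the check at the shared assessments is worded around an intervention TAU does not receive

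*Protocol*

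**What the plan says.** Four parts of the Protocol bear on this.

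- **Safety considerations.** Custodial health nurses engage participants "at each assessment or the start of each BA session to check how they are feeling" and ask "if they experienced any unexpected effects of the intervention". All adverse events go to the trial steering committee. If it considers that they result from the intervention, the trial is suspended.
- **Ethical considerations.** A further enquiry is tied to sessions: "After each prisoner has completed each session of BA, the custodial health nurses will ask them about their emotional well-being", together with whether they have experienced distress.
- **Intervention sections.** The BA arm is offered "twelve sessions of BA, which will be delivered twice weekly, in 30-minute sessions, for six weeks". Of the TAU arm the Protocol says: "No other specific intervention will be provided to this group".
- **Outcomes.** Clinical outcomes are measured "a) at baseline (0 weeks), (b) at 6 weeks post-intervention, and (c) at 3 months post-intervention", so both arms have two assessments after randomisation. Random treatment allocation and blinding gives the collection of these data to the research trial nurse. The Feasibility list includes "The number of adverse events and harms that occur during the trial", and the ninth objective for people in custody is the same count. Neither place states a comparison between arms.

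**The concern.** How many adverse events are recorded depends on how often, by whom and in what words people are asked. Here the schedule differs by arm. BA participants are asked at sessions over six weeks; TAU participants have no scheduled contact outside the two assessments.

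Those two assessments are also a weak source for TAU. The check asks about effects of the intervention, which a TAU participant cannot meaningfully answer. It is assigned to custodial nurses, while the assessment is carried out by someone else. Read literally, it is unclear that a TAU participant would be asked a usable question at either visit.

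This matters in two ways. If the count is shown by arm, as readers of a randomised trial will expect, the columns reflect different amounts of asking. And the steering committee has to judge whether events result from BA. TAU is the trial's only internal evidence of how much distress arises in custody anyway, and the plan as written would under-record it.

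**Working it through.** **Inputs from the Protocol.** Twelve sessions (BA tele-trial intervention group); two assessments after randomisation (Clinical outcome measure- depression); about 30 participants per arm (Sample size). The session figure reproduces: 2 per week × 6 weeks = 12.

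**Scheduled enquiries per participant after randomisation.** With s sessions attended, BA has s + 2 if only the start-of-session check counts, and 2s + 2 if the post-session question counts too. TAU has 2.

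| Sessions (source) | BA, start only | BA, start and end | TAU | Ratio |
| --- | --- | --- | --- | --- |
| 12 (intervention section) | 14 | 26 | 2 | 7 to 13 |
| 10 (quality-of-life section) | 12 | 22 | 2 | 6 to 11 |
| 6 (completion minimum in Objectives and Feasibility) | 8 | 14 | 2 | 4 to 7 |

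The 10 comes from "Completion of eight (8) out of 10 sessions will be deemed to constitute treatment engagement and completion", which conflicts with the twelve sessions offered and with the six-session minimum. Those passages must be reconciled in their own right, but the imbalance is present under each of them.

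**What the imbalance could do to recorded events.** The Protocol gives no adverse event rate and no capture rate, so this step is illustration only. Assume equal true risk in both arms, and let c be the chance that a single contact elicits an event that has occurred. With k contacts remaining after the event, the chance that it is recorded is 1 − (1 − c)^k. Take k = 8 in BA (6 remaining sessions plus 2 assessments) and k = 2 in TAU. For an assumed true risk of 20%, there are 30 × 0.20 = 6 true events per arm.

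| c | Recorded, BA | Recorded, TAU | Expected counts, BA vs TAU | Ratio |
| --- | --- | --- | --- | --- |
| 0.1 | 0.570 | 0.190 | 3.42 vs 1.14 | 3.0 |
| 0.2 | 0.832 | 0.360 | 4.99 vs 2.16 | 2.31 |
| 0.3 | 0.942 | 0.510 | 5.65 vs 3.06 | 1.85 |
| 0.5 | 0.996 | 0.750 | 5.98 vs 4.50 | 1.33 |
| 0.9 | 1.000 | 0.990 | 6.00 vs 5.94 | 1.01 |

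The ratio does not depend on the assumed 20%, which cancels. It is large for mild events that surface only if someone happens to ask at the right time, and nearly 1 for events that would come to light at almost any contact.

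**After the fix.** With identical questions at the two shared assessments, enquiries behind any comparison are 2 against 2, and the expected ratio under equal true risk is 1.0.

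**The case against.** The strongest reply is that the Protocol plans no comparison. It promises a number of events during the trial, and Statistical analyses is descriptive, with effect sizes and GEE reserved for the outcome measures. A trial-wide count is not distorted against one arm. That stands. A reader might infer that a planned outcome is biased against BA; the text does not support that. The difficulty arises only when the count is split by arm or TAU is used as background.

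Second, the enquiry does cover each assessment, so TAU is not without scheduled contact, and reporting to the steering committee is not limited to one arm. This also stands. A reader might infer that the arms cannot be compared at all; the two shared visits show that they could be, if the same question were asked there. As written it is not.

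Third, the session checks are largely for participant care. The post-session question leads to support under a distress protocol that is not shown, and the Protocol does not say that each answer is logged as an adverse event. So 26 is an upper reading. The start-of-session check still leaves 14 against 2.

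Fourth, it is tempting to conclude that ordinary distress in custody will be taken for harm from BA. The documents do not say that the steering committee judges by a ratio between arms, and the Tele-trial Steering Group includes two independent members. What can be said is that its background evidence would be thin.

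Finally, how events are tabulated is commonly left to an analysis plan. True, but who asks what, and when, is trial conduct fixed in this document, and no later tabulation can reliably recover TAU events that were never asked about.

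**Conclusion.** The concern holds in a limited form. Scheduled enquiry is unequal: 14 against 2 per participant at twelve sessions, 26 against 2 if the post-session question is counted, and still at least 8 against 2 at the six-session minimum. At the only shared contacts, the wording does not fit TAU, and the person named to ask is not the person collecting the data. The counts assume that every scheduled contact takes place.

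The consequence is a tendency to over-record mild, elicited events in BA relative to TAU, which weakens any by-arm reading and any use of TAU when judging attribution. Its size cannot be fixed from the documents. The range of about 1.0 to 3.0 rests wholly on the assumed capture chances and on the assumed 8 and 2 remaining contacts. Events that come to light whenever they occur are little affected. This is an inexpensive improvement to make before recruitment, not a defect that makes the planned count unusable.

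**What to change.** In Safety considerations, have the tele-trial nurse ask both arms the same adverse event questions at the 6-week and 3-month assessments, worded neutrally and without reference to the intervention. Record the source of each event: session, assessment or spontaneous report. Base any between-arm description on the assessment-elicited events, and report session-elicited BA events separately, marked as having no TAU counterpart. The session checks for participant care and the suspension rule stay as they are.

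The cost is a few added items at two visits that already take place. The drawback is that the comparative count leaves out some minor events seen only at BA sessions; these still appear in the separate listing.
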